### Laboratory procedures

All respiratory samples including gastric aspirate (diagnostic or treatment monitoring samples) will undergo Xpert Ultra and Mycobacterium Growth Indicator Tubes (MGIT) liquid medium and incubated in the Bactec MGIT 960 mycobacterial detection instrument (Becton Dickinson Microbiology System, BD, USA) and, if available, solid culture (comparator tests). All assays will be performed within 24 h of collection at the reference laboratories (CISM, MU and Eswatini BSL 3.

Results will be interpreted following manufacturer. Following the molecular assays, cultures will be performed. Raw samples will be decontaminated by applying the Kubica method [34]. From the decontaminated pellet, 500 µl will be inoculated into liquid medium* (Mycobacterium Growth Indicator Tubes*—MGIT) and incubated in the Bactec MGIT 960 mycobacterial detection instrument (Becton Dickinson Microbiology System, BD, USA), and 200 µl will be inoculated into solid media (Lowenstein_Jensen—LJ). After 42 days without growth (for MGIT), or 8 weeks (for LJ), cultures will be classified as negative.

All stool samples (for diagnosis or treatment monitoring) will undergo qPCR and Xpert Ultra testing. DNA will be extracted from 50 mg of stool using the MP FastDNA for Soil Kit (MP Biochemicals) in preparation for the stool qPCR. In brief, ethanol will be removed and 50 mg of stool are homogenized using bead-beating with 100μL of DNA eluted by the MPFast DNA soil kit. *Mtb*-specific primers and black hole quencher FAM-labeled minor groove binder probes have been selected from previously described *M. tb*-specific IS6110 sequences [35]. Of note, our qPCR incorporates a control for extraction/PCR inhibition. Stool will be aliquoted, frozen at -80 °C and run in batches at study-specific labs in Mbabane (Baylor COE), Manhica (CISM), and Makerere University (MU). Xpert Ultra will be performed following the KNCV simple one-step (SOS) method [36]. Results will be interpreted following manufacturer guidelines.

Lateral flow urine lipoarabinomannan assays (LF-LAM) from Abbott® will be performed in participants with presumptive TB and confirmed HIV infection in line with the most recent WHO guidelines [37]. The LF-LAM assay will be performed following manufacturer’s instructions. Urine samples will be preserved in -20ºC for future LF-LAM testing if the test is not immediately available. The remaining urine will be stored at -80º for the biorepository.

### Endpoints

#### Definitions

For analysis, the participants in the pediatric cohort will be classified as ‘confirmed tuberculosis’, ‘unconfirmed tuberculosis’ and ‘unlikely tuberculosis’ according international consensus pediatric endpoint definitions [22].  “TB case” definition will include both ‘confirmed’ and ‘unconfirmed’ tuberculosis. “Unlikely TB” will be used as reference for specificity (see Table 2).

**Table 2 Tab2:** Definitions for the pediatric cohort

**TB case**	**“Confirmed tuberculosis”**	*M. tb* to be laboratory-confirmed (culture or NAAT-based assay) from at least 1 specimen or positive urine LAM
	**“Unconfirmed tuberculosis”**	Bacteriological confirmation not obtained and at least 2 of the following: 1. symptoms/signs suggestive of tuberculosis, 2. chest radiograph consistent with tuberculosis, 3. close tuberculosis exposure or immunologic evidence of *M. tuberculosis* infection 4. positive response to tuberculosis treatment (requires documented positive clinical response on tuberculosis treatment—no time duration specified)
**Not TB case**	**“Unlikely tuberculosis”**	bacteriological confirmation not obtained and criteria for “unconfirmed tuberculosis” not met

For the adult cohort participants will be classified as “bacteriologically confirmed TB” or “clinically diagnosed TB”. “TB case” definition will be equivalent to decision to start treatment irrespective of bacteriological confirmation so it will include both “bacteriologically confirmed TB” and “clinically diagnosed TB”

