## Methods

### Aim and objectives

The primary objective of the Stool4TB study is to evaluate the diagnostic performance of the stool bead-based real-time quantitative PCR (qPCR) platform for TB diagnosis in children < 8 years and PLHIV compared to a composite reference standard that includes sputum (induced sputum and/or gastric aspirate in children) and stool Xpert Ultra, sputum (induced sputum and/or gastric aspirate in children) culture, and urine LF-LAM (among people living with HIV).

As a secondary objective, we will compare the diagnostic accuracy of the novel stool qPCR assay to the other tests against clinical diagnosis and a bacteriological reference standard [22]. We will also evaluate the quantitative stool qPCR platform as a tool to monitor treatment response in these two populations. Samples collected from these cohorts will be used to develop a biorepository of well characterized samples to enable future TB related research as an exploratory objective.

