#### Primary endpoint

Sensitivity and other test parameters, such as specificity, positive predictive value (PPV) and negative predictive value (NPV), of the qPCR test will be calculated with respect to a composite reference standard including any of the other tests (induced sputum and gastric aspirate Xpert Ultra and MGIT culture, stool Ultra or TB-LAM in HIV-positive individuals).

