### Data synthesis and analysis

We will summarize demographic characteristics of the samples and will perform a descriptive analysis of endpoints and other relevant clinical variables. Quantitative variables will be summarized using means, standard deviation, median and interquartile range. Categorical variables will be analysed using frequencies and proportions. We will analyze the mechanisms that contribute to missing data, which will guide subsequent imputation methods to address missingness. An accuracy analysis will be performed for both study groups (children and PLHIV) with bacteriologically confirmed tuberculosis as a reference standard and qPCR assay on stool as the index test under evaluation. We will calculate sensitivity *(primary endpoint)* and other test parameters: specificity, PPV and NPV, of the qPCR test compared to composite reference standard that includes any of the other tests positive (including induced sputum and gastric aspirate Xpert Ultra and MGIT culture, stool Ultra or LF-LAM). We will also calculate sensitivity (and other parameters: specificity, PPV and NPV) of the qPCR test *(secondary endpoint)* with respect to a clinical case definition. Accuracy will also be assessed for stool qPCR and each of the other microbiological confirmation tests separately against the clinical case definition (*secondary endpoint)*, in order to compare the performance of each test.

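### As written, Table 2 lets the index stool qPCR confirm TB in children, so specificity and PPV in the pediatric secondary analysis against TB case would be 100% by construction

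*Protocol article*

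**What the plan says.** All references are to the protocol article.

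- **Definitions, Table 2.** Confirmed tuberculosis in a child requires M. tb "to be laboratory-confirmed (culture or NAAT-based assay) from at least 1 specimen or positive urine LAM". Unlikely tuberculosis means "bacteriological confirmation not obtained and criteria for “unconfirmed tuberculosis” not met". TB case is the sum of confirmed and unconfirmed. The text above the table says that the unlikely-TB group "will be used as reference for specificity".
- **Laboratory procedures.** "All stool samples (for diagnosis or treatment monitoring) will undergo qPCR and Xpert Ultra testing". The qPCR targets IS6110, so it is a nucleic acid amplification test on a specimen.
- **Secondary endpoints.** Sensitivity, specificity, PPV and NPV of the qPCR are calculated against TB case, which for children is defined only through Table 2.
- **Aim and objectives.** The qPCR is "compared to a composite reference standard that includes sputum (induced sputum and/or gastric aspirate in children) and stool Xpert Ultra", respiratory culture and urine LF-LAM. The qPCR is not in that list.
- **Primary endpoint.** Accuracy is calculated "with respect to a composite reference standard including any of the other tests", followed by a list of Ultra, culture and LAM.
- **Data synthesis and analysis.** The accuracy analysis is run "with bacteriologically confirmed tuberculosis as a reference standard and qPCR assay on stool as the index test". The next sentence again describes a composite of the other tests.

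**The concern.** A test cannot be judged fairly against a reference that contains its own result. If a positive stool qPCR alone makes a child a confirmed case, every false positive in a child without TB is relabelled as a true positive. The group used for specificity is emptied of qPCR positives before specificity is calculated, and the estimate says nothing about the assay.

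This matters most for the secondary analysis against TB case. Specificity there should show how often a new, more sensitive stool assay is positive in children whom follow-up shows to be without TB. A literal application of Table 2 would return 100% for specificity and PPV, and a reader could take those figures as evidence.

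The wording elsewhere does not settle the matter for an analyst who works from Table 2. The Secondary endpoints section groups the qPCR with the other microbiological confirmation tests, and the Background presents it as a tool for bacteriological confirmation. The Discussion says that unlikely TB is limited to participants who tested negative at baseline, without saying on which tests.

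**Working it through.** **1. The plan's own figure.** From Power and sample size: sensitivity 80%, precision 7.5%, laboratory-confirmed share 8.5%. A two-sided 95% normal interval is assumed, because the confidence level is not stated.

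- Cases needed = 1.96² × 0.80 × 0.20 / 0.075² = 109.3, rounded up to 110.
- Children needed = 110 / 0.085 = 1294.1, rounded up to 1295, as stated.

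The plan thus expects 110 children positive on the composite, 88 of them qPCR-positive (0.80 × 110), and about 1185 composite-negative (1295 − 110).

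**2. The rule followed literally.** The qPCR is a NAAT on stool. A qPCR-positive child therefore meets the confirmed rule, has bacteriological confirmation, and cannot be unlikely TB. The number of qPCR positives in the specificity group is zero. Specificity = (all unlikely) / (all unlikely) = 100%, and PPV against TB case = 100%. This needs no numerical assumption.

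**3. Size, by illustration.** Assumed inputs:

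- The 1185 composite-negative children split into 800 unlikely and 385 unconfirmed. The document gives no source for this split.
- 19% of the unconfirmed are qPCR-positive: 0.19 × 385 = 73. This is the pilot figure in the Background for children negative by sputum Xpert, a less strictly tested group than composite-negative children.
- True specificity is 96% to 99%, giving (1 − 0.96) × 800 = 32 or (1 − 0.99) × 800 = 8 false positives.

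With the qPCR excluded, TB cases number 110 + 385 = 495, of whom 88 + 73 = 161 are qPCR-positive. With the qPCR counted, the false positives join both figures.

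| True specificity | False positives | Specificity, qPCR excluded → counted | PPV, excluded → counted | Sensitivity against TB case, excluded → counted |
|---|---|---|---|---|
| 99% | 8 | 99% → 100% | 161/169 = 95.3% → 100% | 161/495 = 32.5% → 169/503 = 33.6% |
| 96% | 32 | 96% → 100% | 161/193 = 83.4% → 100% | 161/495 = 32.5% → 193/527 = 36.6% |

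The sensitivity shift is small because qPCR-positive unconfirmed children are TB cases either way. NPV does not change in this calculation, since qPCR-negative children stay where they are (495 − 161 = 503 − 169 = 527 − 193 = 334 missed cases).

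**4. The primary composite.** Here a child positive on qPCR only is a false positive. If 1%, 2%, 5% or 10% of the 1185 composite-negative children were qPCR-positive (about 12, 24, 59 or 118), specificity would be 99%, 98%, 95% or 90%. It is free to vary, so the primary analysis is not forced.

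**The case against.** The strongest reply is that Table 2 is silent on the index test and does not name it, and that the rest of the article shows the intent. The objectives list the reference components without the qPCR. The primary endpoint and the analysis section speak of the other tests. The sample size uses the laboratory-confirmed share as the prevalence for sensitivity against that composite, and 1295 reproduces on that basis. The Discussion treats children negative on every other test but qPCR-positive as a separate additional yield, which fits poorly with their already being confirmed cases. Table 2 follows consensus definitions, so its mention of NAAT-based assays may be generic wording.

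Most of this stands, and it limits the point in three ways.

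- A reader might infer that the trial's specificity as a whole is 100% by definition. The documents do not support this, because the primary reference excludes the qPCR. The analysis section names the confirmed reference and the index test as separate things, then gives the other-tests composite.
- A reader might infer that sensitivity climbs from 80% to 88–90%: (88 + 73 + 8)/(110 + 73 + 8) = 169/191 = 88.5%, up to 193/215 = 89.8%. That uses a confirmed class containing the qPCR, which none of the listed endpoints takes as its reference.
- A reader might extend the point to adults. The adult TB case rests on the decision to start treatment and has no NAAT rule.

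The reply does not remove the point. The other-tests wording governs the primary composite, while the pediatric TB case comes from Table 2 alone. Nor is this merely a detail that a condensed article leaves to the full protocol: the definition is stated, and its plain words conflict with the reference standard stated elsewhere.

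**Conclusion.** The point holds as a conflict of wording with a definite consequence if Table 2 is applied as printed. Table 2 literally admits the index qPCR as a confirming test, against the objectives, primary endpoint and analysis sections. The consequence is confined to the pediatric secondary analysis against TB case. There, specificity and PPV become 100% by construction. Under the inputs shown, PPV should be about 83–95%, and sensitivity is inflated by roughly 1 to 4 percentage points (32.5% to 33.6–36.6%).

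The 100% result follows from the rule alone. The other sizes rest on an unsourced 800/385 split, a pilot positivity figure from a somewhat different group, and an assumed true specificity of 96–99%, so they are illustrations only. The authors probably intend to exclude the qPCR, which makes the correction uncontroversial. The primary endpoint, the sample size and the adult TB-case rule are not affected.

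**What to change.** 1. In Table 2, state that laboratory confirmation is by culture, Xpert Ultra or LF-LAM, excluding the index stool qPCR.
2. State that classification as confirmed, unconfirmed or unlikely tuberculosis is made without qPCR results.
3. In the Discussion, make clear that testing negative at baseline refers to those same tests.
4. Keep children positive on qPCR only as the separate additional-yield category that the Discussion already describes.

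The cost is a few words in Table 2 and matching text in the analysis plan. No new data are needed and the sample size stays at 1295 children. In return, pediatric specificity and PPV against TB case become real estimates.

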### Study design

This is a multi-national, prospective, diagnostic evaluation study with a nested longitudinal cohort evaluation. The total duration of the study will be 60 months, with a 30-month recruitment period in which different samples will be collected at baseline to assess the diagnostic performance of the qPCR assay. Recruitment in adults began November 2021 and will end by May 2024. In children recruitment began in April 2022 and will end by September 2024. All participants initiating TB treatment will be followed until treatment completion in order to assess treatment outcomes and the potential of the qPCR assay to be used as a treatment monitoring tool. Those participants not initiating TB treatment will be followed for 2 months after recruitment to accurately rule out TB diagnosis.

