### Study visits, assessments and clinical procedures

After written informed consent has been obtained from the adult participants or the children’s guardians, the study clinician or nurse will perform a full anamnesis, complete the clinical evaluation, obtain a chest X-ray (AP/PA and lateral for children) and conduct sampling for bacteriological confirmation. For children, 2 respiratory specimens (either induced sputum, gastric aspirate or nasopharyngeal aspirate), 1 urine sample (for those living with HIV) and 1 stool sample will be collected as soon as possible. In the adult cohort, only one sputum sample will be required. Blood samples will be collected if HIV test has not been performed in the last 6 months in children, and if viral load and CD4 count has not been performed in those PLHIV in the previous 3–6 months, and TST/IGRA will be performed at baseline, if available (see Table 1 for Schedule of events, SoE).

Those participants not starting ATT will be referred to routine services for clinical management and a study clinical follow-up visit will be conducted at 2 weeks and 2 months to ascertain the TB free phenotype. If the participant is still symptomatic by two months of follow-up, full resampling and clinical assessment will be done as detailed in the schedule of events (Table 1). Parent(s)/guardian(s) are invited to bring their child back to the hospital in case of new symptoms for an unscheduled (extra) visit. The decision to start ATT will be made by either healthcare system doctors or study clinicians in accordance with the local guidelines at each of the sites.

**Table 1 Tab1:** Schedule of events

	**Baseline**	**Week 2**	**Month 2**	**Months 4**	**Month 6**

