**PRESUMPTIVE TB**					
Past medical history	X				
TB exposure assessment^a^	X		X		
Full clinical assessment	X	X (tel adults)^b^	X		
CD4, HIV viral load (if HIV positive)^c^	X				
Chest X-Ray	X				
Diagnostic Samples	X		if symptoms		
SPUTUM (ultra, culture, Biorepository)					
STOOL (ultra, qPCR, Bio)					
URINE (LAM, bio)					
Blood^d^	IC (60)				
**TB CASE**^**e**^					
Clinical assessment	X	X	X	X	X
Chest X-Ray					X
ATT response (sputum, stool)		cTB	cTB	cTB	cTB
Blood^d^	cTB (200)	cTB (200)		cTB (200)	cTB (200)

*IC* Ill controls, *cTB* confirmed TB

^a^ TB exposure assessment will be performed via questionnaire in every participant and TST/IGRA will be performed at baseline if available on site

^b^On week 2, the clinical assessment will be performed by telephone in adults without symptoms

^c^If HIV infected and have not had VL and CD4 count in the last 3 months. Up to six months VL and CD4 counts will be accepted

^d^Blood (PAXgene, QF, serum): QuantiFERON will be collected in baseline and four months for those starting treatment and at baseline in 60 ill controls (10 pressumptive TB participants that do not meet the criteria for TB disease per category and site). PAXgene and serum will be collected at baseline, week 2, month 4 and month 6 for those starting treatment, and at baseline in 60 healthy controls

^e^If a decision is made to start ATT after the baseline visit, the schedule of follow-up visits should be adapted so that the TB treatment start date will be the new “baseline” date

For those starting ATT, follow-up will be conducted until the end of treatment with visits at 2 weeks, 2 months, 4 months and 6 months after ATT initiation (and an extra visit at the end of treatment if the treatment lasts more than 6 months). Among people who have bacteriologically confirmed TB, one respiratory sample, one stool sample and a urine sample will be collected at each follow-up visit until negative bacteriological samples have been obtained for at least two consecutive visits. Chest X-ray will be performed at the end of ATT.

Blood will be collected in those bacteriologically confirmed at the start of ATT, week 2 post ATT, month 4 post ATT and at the end of treatment to conduct treatment monitoring mRNA signatures. After study sampling is completed according to the schedule of events (Table 1), remaining samples will be stored in a biorepository for use in future exploratory TB research.

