## Discussion

This study is designed to evaluate a new diagnostic test that aims to improve molecular confirmation of TB as well as provide a new monitoring tool for treatment response in children and PLHIV. To date, studies using stool as a target sample have been done with already existing molecular tests like Xpert and Xpert Ultra using stool, but few of those studies propose novel molecular platforms for validation or exclusively include the vulnerable populations of intended use (children or PLHIV with presumptive TB). Therefore, the relevance of this study relies not only on the use of stool as a sample for bacteriological confirmation, but also on the molecular non-Xpert based approach to it, as there is need for improvement molecular stool diagnostics. Further, the design is aligned with the latest WHO guidelines on diagnosis and management of TB in children and adolescents that, for the first time, include stool as a valid sample for TB testing. In fact, apart from the classical approach of using culture in a respiratory sample as a reference standard, we will assess the performance of this new diagnostic test against a robust composite reference standard that includes culture and Xpert Ultra in respiratory samples, Xpert Ultra in stool and LF-LAM in urine and against clinical diagnosis. In this way, we will both maximize the bacteriological confirmation and estimate the potential increase in bacteriological confirmation in those cases that start treatment in the absence of bacteriologic confirmation. It will also allow to see the contribution of each single TB test to bacteriological confirmation, including the expected additionality of que novel stool-based qPCR (all other test negative but qPCR positive).

Another relevant strength in the study design is the two week and two-month longitudinal follow-up to verify baseline disease classification in participants who do not initiate treatment. This will play a relevant role in both increasing the number of confirmed cases (after resampling if persistence of symptoms), but also in the reliability of the specificity estimations (only those who have tested negative at baseline, who did not start treatment and who do not present symptoms after 2 months will be classified as “unlikely TB”).

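### The adult 'TB case' reference for the two secondary accuracy endpoints equals the decision to treat, with no stated way out for treated adults in whom TB is later excluded

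*Protocol article*

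**What the plan says.** **Adult reference.** Under Endpoints, Definitions, the adult 'TB case' "definition will be equivalent to decision to start treatment irrespective of bacteriological confirmation", so it pools bacteriologically confirmed and clinically diagnosed adults. Under Study visits, "The decision to start ATT will be made by either healthcare system doctors or study clinicians in accordance with the local guidelines" of each site.

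**Where it is used.** Secondary endpoints takes 'TB case' as the reference for qPCR accuracy, and again for qPCR and each other microbiological test separately. Primary endpoint uses the composite of the other tests, which does not involve the treatment decision.

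**Who is verified.** The Discussion describes "longitudinal follow-up to verify baseline disease classification in participants who do not initiate treatment". On the class 'unlikely TB', it adds that "only those who have tested negative at baseline, who did not start treatment and who do not present symptoms after 2 months will be classified" in that way. Study design says that those not starting treatment are "followed for 2 months after recruitment to accurately rule out TB diagnosis". For treated participants it gives a different purpose: "All participants initiating TB treatment will be followed until treatment completion in order to assess treatment outcomes" and the qPCR as a monitoring tool.

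**Changes after baseline.** Table 1, footnote e: "If a decision is made to start ATT after the baseline visit, the schedule of follow-up visits should be adapted". This covers movement from untreated to treated. No passage describes the reverse.

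**Adult non-cases.** The Abstract names a third adult class, 'not TB'. Definitions lists only the two adult case classes and does not define it.

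**The concern.** A treatment decision is often taken before all the evidence is in. Culture alone may need 42 days (MGIT) or 8 weeks (LJ) before it is called negative. Some adults who start empirically may later receive another diagnosis that excludes TB. Under the stated definition they remain in the denominator of sensitivity, and a correct negative qPCR is scored as a miss. The same happens to each comparator.

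At stake is what the adult secondary sensitivities mean. They would partly reflect how readily clinicians at each site treat empirically, which may differ among three countries working to local guidelines. The visits at which a revised diagnosis would become known are already scheduled for everyone on treatment (week 2 and months 2, 4 and 6).

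For untreated adults there is a smaller problem of wording. Definitions implies that no treatment means no case, whereas the Discussion asks for a symptom-free check at 2 months. Its label, 'unlikely TB', is the paediatric one.

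**Working it through.** **1. The plan's own figure.** The sample size is for sensitivity against the composite: cases = z² × Se × (1 − Se) / d², divided by the proportion confirmed.
- Children: 1.96² × 0.8 × 0.2 / 0.075² = 109.3, rounded up to 110; 110 / 0.085 gives 1295, as stated.
- Adults: 1.96² × 0.8 × 0.2 / 0.07² = 125.4, rounded up to 126; 126 / 0.20 = 630. The stated 650 gives 650 × 0.20 = 130 cases and a half-width of 1.96 × √(0.16 / 130) = 6.9%, which meets the 7% target.

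Neither figure uses 'TB case', so this point changes neither.

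**2. Inputs for an illustration.**
- Confirmed adults: 130, from step 1, with 80% qPCR-positive (Power and sample size).
- Clinically diagnosed adults: 130. This is an assumption, from the Background remark that culture confirms about half of PLHIV starting treatment.
- qPCR-positive among the clinically diagnosed: 12% (pilot in Eswatini adults, Background).
- Share g of the clinically diagnosed who are qPCR-negative and in whom TB is later excluded: assumed 5-20%. The documents give no figure.

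**3. Sensitivity as the definition would score it.**
(0.80 × 130 + 0.12 × 130) / 260 = (104 + 15.6) / 260 = 119.6 / 260 = 46.0%.

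**4. Sensitivity with those adults removed from the cases.**

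| g | Adults removed | Sensitivity | Understatement |
|---|---|---|---|
| 5% | 6.5 | 119.6 / 253.5 = 47.2% | 1.2 points |
| 10% | 13 | 119.6 / 247 = 48.4% | 2.4 points |
| 20% | 26 | 119.6 / 234 = 51.1% | 5.1 points |

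**5. How firm is this?**
- If 5% of the removed adults were qPCR-positive, the last row becomes (119.6 − 1.3) / 234 = 50.6%, or 4.6 points.
- If the clinically diagnosed group were half as large (65), the starting value is (104 + 7.8) / 195 = 57.3%. The range becomes 111.8 / 191.75 = 58.3% to 111.8 / 182 = 61.4%, or 1.0-4.1 points.

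**6. Effect on comparators.** The removed adults are bacteriologically negative, so no comparator loses a positive result. If they are qPCR-negative too, every test's sensitivity is multiplied by the same factor, for example 260 / 247 = 1.05 at g = 10%. Ratios between tests are then unchanged; absolute values, and absolute differences between tests, are understated.

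**The case against.** **Silence is not a rule.** A reader might infer that adult status is fixed for good at treatment start and never revised. No passage says so. The article condenses a full protocol, and an adjudication rule may stand there or in the SAP. Footnote e also shows that status can change in one direction. This objection stands against the strong reading. It does not remove the point, because the article states a positive equivalence, and its description of verification leaves out treated participants. An adjudication rule elsewhere would have to qualify that published wording.

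**The definition suits one stated purpose.** The Discussion wants the added confirmation among people who start treatment without bacteriological proof. For that question the treated group is the target population. This stands, and it is why the current definition should still be reported.

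**Children are not handled better.** One might infer from Table 2, whose fourth criterion is "positive response to tuberculosis treatment (requires documented positive clinical response on tuberculosis treatment", that a child's class is corrected by what happens on treatment. That criterion only adds evidence towards a case. Table 2 contains no removal rule, so it offers no precedent.

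**The size is assumed.** This stands. No rate of later exclusion is given. The 'about half' refers to culture alone, whereas this study adds Xpert Ultra and LF-LAM, so the clinically diagnosed share may be smaller. The 12% comes from sputum-Xpert-negative adults, not from adults negative on the whole composite.

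**Untreated adults.** One might infer that test-negative adults who die or are lost before 2 months become non-cases and bias specificity. The documents do not say this. Someone not seen at 2 months does not demonstrably meet the Discussion's condition, and a missing-data analysis is planned. Only the mismatch of wording remains.

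**Conclusion.** The point holds for the adult secondary accuracy endpoints. Followed as written, the definition and the Discussion's account of verification leave a treated, bacteriologically negative adult in whom TB is later excluded among the cases. Sensitivity against 'TB case' falls whenever qPCR is positive less often in such adults than in true cases.

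The documents cannot give the size. Under the assumptions shown it is about 1-5 points, somewhat less if fewer adults are diagnosed clinically, and nil if no such adults occur.

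It would be wrong to conclude that the trial's main qPCR sensitivity is biased: the primary endpoint and sample size are untouched. Nor is the effect a handicap peculiar to qPCR, since all tests share the reference. This is a modest flaw in a secondary reference standard and is cheap to put right before analysis.

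**What to change.** These changes concern analysis classification only and leave clinical management as it is.

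1. Assign the adult class at the end of the follow-up already scheduled, blind to the qPCR result.
2. Class a bacteriologically negative treated adult as 'not TB' if a documented alternative diagnosis excluded TB. If this is unclear, class the adult as unclassifiable, outside both denominators.
3. Report the secondary accuracy results under the treatment-decision definition alongside.
4. Define the adult 'not TB' class in Definitions. Reconcile the implied rule there (no treatment, hence no case) with the Discussion (symptom-free 2-month check required), and state that the check applies to adults too.

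The cost is a change of wording and a field for the alternative diagnosis at existing visits. The downside is that a few adults leave the case denominator. Known comparator results may also influence the judgement that TB was excluded, which is a further reason to show both versions. If the full protocol or SAP already has such a rule, a cross-reference is enough for items 1 and 2.
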